## Abstract

The transition to primary school is a key milestone in a child’s life and how ready a child is for this change can affect their later academic success. Executive functions are regarded as an important contributor to school readiness, and the early development of executive functions are strongly moderated by the child’s social context, such as caregiver relationships. Whilst the role of parent-child relationships on the development of executive functions is well established, less is known about the role of other caregivers, such as teachers. A series of novel teacher-child electroencephalography hyperscanning interaction tasks have been developed to explore how teachers scaffold preschool children’s emerging literacy skills, problem solving and executive functions. Behavioural and neural synchrony will be measured during interactive tasks. Children’s school readiness will be measured, as well as teacher and child executive functions and intelligence. The relative contribution of the teacher and child’s individual characteristics to behavioural neural synchrony will be explored, as well as the effects teacher scaffolding style. These insights are necessary to ensure the quality of infant care and preschool in a climate where attendance is becoming increasingly popular worldwide.

## Introduction

A successful transition to primary school is an important milestone in a child’s life, which places increasing demands on their executive functions (EFs). EFs are cognitive processes involved in the control and coordination of information which assists goal-directed behaviour [1]. A child might use EFs to remember and follow the teacher’s instructions, complete tasks independently and to smoothly transition between tasks, as well as to stay on task and ignore distractions. There are individual differences in how ready children are to learn in structured environments and EFs have been reported to be the single best predictor of school readiness [2,3]. This highlights the importance of EFs in child development and the importance of understanding which factors promote development of EFs in preschool children.

Interaction between teachers (also referred to as educators or caregivers in some contexts) and children (or students) are thought to be an important factor in the development of preschool children’s EFs. This is supported by research reporting the efficacy of using story books and puzzles to scaffold the development of children’s EFs [4]. Howard and colleagues reported that storybook reading improved preschool children’ s working memory and shifting abilities [4]. Furthermore, links between teacher-child relationships and academic performance have been reported in primary school children [5,6]. A previous meta-analysis of 23 independent samples, which were predominantly adults, reported that interpersonal neural synchrony was positively associated with learning outcomes [7]. Interpersonal neural synchrony is defined as correlation or coherence in time, space and/or frequency dimensions between two communicating brain signals [7,8]. It is unclear exactly *how* preschool teachers support development of children’s EFs; therefore, the current investigation will explore the potential involvement of neural synchrony in teacher-child interactions that support development of EFs.

### School readiness and executive functions

The age children start school varies across countries, but in Singapore children begin primary school around age 6 or 7 years. Prior to this, it is increasingly common for Singaporean children to attend infant care and preschool, as is also true in many countries worldwide. This presents an invaluable opportunity to not only prepare children for primary education, but also to potentially reduce gaps among children from disadvantaged home environments. Schools place increasing demands and expectations on children and require them to engage in formal structured learning activities. It is important to ascertain when children are ready for this next step. School readiness is a multidimensional construct that comprises cognitive, language, social-emotional-behavioural, physical and learning skills that enable children to learn and thrive in a school [9,10]. School readiness has been measured in terms of the understanding of basic concepts including colours, letters, numbers, shapes and social-emotional competence [11], as well as in terms of (pre-)academic abilities including (emerging) literacy skills and (emerging) mathematical knowledge [12]. Children vary in their school readiness and the extent to which children are ready for school when they start schooling has significant impacts on their social and academic achievement trajectories [13–17].

EFs are a constellation of partially dissociable higher-order cognitive processes that allow goal-directed behaviour. Significant development of EFs occurs between the ages of 3 and 5 years [18], which is the age which many children attend preschool. EFs play a significant role in the ability to regulate attention, emotion and behaviour in preschool children, which are essential for successful engagement in the classroom [19]. EFs provide a foundation for academic achievement and school performance by contributing to the children’s social functioning, emotion regulation and intentional learning [20]. This is exemplified by evidence that EFs are associated with children’s academic trajectories [13,21,22]. Cameron and colleagues report evidence for co-development of EFs and academic skills with improvements in EFs being associated with improvements in applied problem solving in 5 year old children, EF sub-domains were not assessed separately in this investigation [21]. Furthermore, EFs have long-term effects impacting several domains including academic success, impulse control, constraint and emotion regulation [23]. Previous intervention research indicates that EFs can be malleable and training of EFs has been linked to early academic success [13,24,25]. This highlights the critical role of EFs in school readiness and wider child development, as well as the importance of identifying factors that support development of EFs and the mechanisms by which this development occurs.

### Teacher scaffolding and interpersonal synchrony

Preschool teachers have a central role in their class’s preschool experience and development. Vygotsky’s [26] sociocultural theory dictates that learning is a social activity that occurs most effectively in social interaction with others. Additionally, children’s learning and development are optimally supported by scaffolding or assistance from more competent individuals [26]. Teachers may scaffold children’s learning by temporarily providing support to the child to allow them to complete a task that they would not be able to complete independently. As the child’s skill level increases, the teacher may gradually withdraw their support as the child becomes more capable until the child can complete the new task independently [27].

Scaffolding has been researched in the context of storybook reading (also referred to as read aloud; see 28) due to the frequency of this activity in preschools [28]. Storybook reading has a predictable, routinised format in which teachers can explore various texts with children, which has been reported to scaffold children’s emerging literacy skills [29]. Dialogic reading is an example of a common scaffolding technique employed during storybook reading contexts. This involves collaborative storytelling, in which the reader identifies and poses problems to the child and then scaffolds their answers [4,30]. Children’s participation in storybook reading sessions has been associated with positive effects of vocabulary growth [31–33] and comprehension [34,35], as well as giving children the opportunity to have more sophisticated conversations, going beyond perceptual understanding of stories and considering conceptual features [36]. Like EFs, children vary widely in their emergent literacy skills. Upon starting school many children know the alphabet, whereas many others do not [37]. To understand *how* children acquire literacy skills from their teacher, a dyadic storybook reading task has been developed to explore how preschool teachers scaffold children’s novel word learning and story comprehension.

One mechanism thought to influence exchange of knowledge between teacher and student is interpersonal neural synchrony*.* It has been theorised that this provides a neural underpinning for interpersonal exchange [38]. Interpersonal synchrony has been suggested to facilitate internal predictions about the self and predictions about the behaviour of others thereby optimising interactions [39]. Neuro-behavioural synchrony is posited to be an optimal learning environment for a child [40]; therefore, the present study aims to explore the contributions of interpersonal synchrony between teacher and child to the child’s learning outcomes.

Neural synchrony has been studied in preschool-age children previously using problem solving tasks. For example, Nguyen and colleagues [41] compared neural synchrony between preschool-age children and their parents when completing Tangram puzzles cooperatively, or independently. Unlike storybook reading, puzzle solving does not have an inherent rhythmicity making it an interesting context in which to study synchrony as synchrony is less likely to be masked by the rhythmicity of the task. Neural synchrony was greater under cooperative conditions and was associated with improved problem-solving performance [41]. Neural synchronisation was reported in temporal brain areas, which have been associated with effective social communication and mentalizing [42,43], as well as frontal areas, which have been previously associated with interactive decision making and EFs [42,43]. This highlights the relationship between EFs and their possible role in establishing neural synchrony or vice versa. The current investigation will use a range of teacher-child interaction tasks to assess the relative contribution of interpersonal neural synchrony to novel word learning and problem solving [44].

### The current investigation

This study will assess the relationship between teacher-child neural synchrony, child development of EFs and school readiness in preschool-age children. Children will be assessed cross-sectionally between the ages of 2 and 7 years. Children will complete EFs, vocabulary and school readiness assessments. Additionally, children and teachers will take part in interactive tasks whilst undergoing dyadic electroencephalography (EEG) and electrocardiogram (ECG) recordings to assess teacher-child interpersonal neural synchrony.

Study objectives and research questions:

Which teacher-child behavioural interaction characteristics are associated with individual differences in preschool children’s executive function and school readiness?Does teacher-child neural synchrony during scaffolded tasks predict learning outcomes, including executive function and school readiness?

Explorative analyses:

Do different forms of teacher scaffolding (e.g., patterns of multimodal ostensive signals or dialogic reading framework) relate differentially to behavioural or neural synchrony?How do teacher individual characteristics (e.g., EF, stress, temperament) moderate the relationship between scaffolding and child outcomes?

The study protocol will be described in eight main sections: study preparation, EFs tasks, school readiness assessment, vocabulary assessment, teacher-child interaction tasks, creative problem solving tasks, neurophysiological measures and questionnaire measures.

### Study preparation

#### Ethics.

This study has obtained ethical approval (IRB-2023-623 & IRB-2025-037) from the Nanyang Technological University Institutional Review Board (IRB). Data collection began in 5^th^ May 2025 and is planned to continue until 31^st^ September 2027 or when the recruitment target is reached. Written consent has been obtained from all adult participants and from the parents or guardians of child participants.

#### Recruitment overview.

Participants will be preschool children aged 2–7 years and previously unacquainted preschool teachers. The selected age range of 2–7 years reflects a critical developmental window during which core executive functions—such as working memory, cognitive flexibility, and inhibition—undergo rapid maturation [18,20]. This range also aligns with the typical age of preschool attendance in Singapore, where children begin preschool as early as age 2 or 3 years and transition to primary school at age 6 or 7 years [45]. Participants will be recruited via collaborations with preschool groups and independent participants. Children and teachers will be invited to the lab for 2 sessions lasting up to 3.5 hours each, ideally less than 2 weeks apart. Teachers will be invited to an additional individual assessment session lasting up to 3 hours. In this session teachers will complete individual EFs and intelligence assessments.

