#### Sample size.

Research question 1 will be addressed using regression methods; therefore, a power calculation has been performed using RStudio (version 2024.04.1 + 748, Posit Software) and pwr library (version 1.30) to obtain an *R*_*2*_ value of 0.09, which is roughly equivalent to a medium effect as Cohen’s *d*. A sample of 187 children would permit the explanation of 9% of the variance with 12 predictor variables, 80% power and 5% chance of type 1 error. To account for attrition an additional 10% will be recruited to give a final sample size of 206 children. Up to 50 preschool teachers will be recruited, but fewer teachers may be required if they elect to take part with several children.

Children and teachers will be eligible if they do not have any identified genetic, metabolic, syndromic, or progressive neurological disorder, (e.g., epilepsy, Down or Rett Syndrome, Autism Spectrum Conditions, Attention Deficit Hyperactivity Disorder, Tuberous Sclerosis, Neurofibromatosis, Fragile X Syndrome,).

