### Analysis plan

A combination of standard regression and machine learning methods will be used to identify characteristics of teacher-child social interactions that significantly predict EFs and school readiness scores (Research Question 1). Examples of behavioural indices of interaction quality are ostensive signals (gaze, speech, gestures), number of teacher prompts used, difficulty level of teacher prompts, number of prompts responded to by the child and complexity of child response. These behavioural indices of interaction quality along with individual teacher and child characteristics, such as personality or temperament, will be used to as factors to predict child EFs and school readiness. Data reduction methods such as least partial squares or principal components analysis may be used to reduce the dimensionality of data and prevent multicollinearity issues. These reduced factors will be used to predict school readiness and EFs.

To explore which characteristics of teacher-child neural coupling are associated with successful teacher-child interactions (Research Question 2) indices of neural coupling will be calculated from the dyadic EEG data and will be analysed in relation to learning outcomes on scaffolding tasks, as well as the behavioural indices of interaction quality that explain the most variance in EFs and school readiness. Examples of indices of neural coupling are weighted phase lag index (wPLI) or partial directed coherence (PDC). wPLI is a non-directional measure of neural coupling which will describe linear dependencies between the phase neural oscillations between two channels. This may be used to measure connectivity within the teacher or child’s brain, as well as between the teacher and child’s brains. PDC, alternatively, is a directed measure of connectivity and will provide additional information about the directionality of the flow of information. We will also explore the extent to which synchrony in the participants ECG is associated with successful teacher-child interactions.

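### Traits of teachers whom the children have not met before are to predict the children's standing executive function and school readiness, which those traits cannot have shaped

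*Protocol article*

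**What the plan says.** Under Recruitment overview, the protocol article describes the sample: "Participants will be preschool children aged 2–7 years and previously unacquainted preschool teachers". Recruitment runs through two routes: "Participants will be recruited via collaborations with preschool groups and independent participants". Contact is brief, as teacher and child are "invited to the lab for 2 sessions lasting up to 3.5 hours each, ideally less than 2 weeks apart".

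The section on the current investigation fixes the timing of the outcomes: "Children will be assessed cross-sectionally between the ages of 2 and 7 years". Under Sample size, "Up to 50 preschool teachers will be recruited", and "fewer teachers may be required if they elect to take part with several children".

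For Research Question 1, the Analysis plan then states that behavioural indices of interaction, along with "individual teacher and child characteristics, such as personality or temperament, will be used to as factors to predict child EFs and school readiness". An exploratory question adds: "How do teacher individual characteristics (e.g., EF, stress, temperament) moderate the relationship between scaffolding and child outcomes".

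The limitations section concedes that scaffolding style is not manipulated and that experimental control is given up for naturalistic interaction. It does not say that a newly met teacher cannot account for what the child could already do.

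**The concern.** The EF tasks and the school readiness screen measure skills built up before the child came to the lab. The screen covers motor, language, personal-social and pre-academic skills. The teacher enters the child's life at the lab session. A stable teacher trait, such as temperament or the teacher's own EF, therefore has almost no causal route to these scores.

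If the regression or a machine learning selection step nevertheless picks out a teacher trait, the result invites a reading as teacher influence. The section on significance speaks of how teacher-child interaction supports EF development, and of uses in policy and in measuring teaching quality. A coefficient that arises from who was paired with whom would be poor evidence for either. The planned data reduction could also fold teacher traits into components together with behavioural indices, and the problem would then be hard to see.

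**Working it through.** **1. The plan's own figure.** Inputs from Sample size: R² = 0.09, 12 predictors, 80% power, 5% type 1 error.

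- f² = 0.09 / (1 − 0.09) = 0.0989.
- With N = 187: u = 12, v = 187 − 13 = 174, noncentrality = 0.0989 × 187 = 18.5. The noncentral F distribution gives power 0.803, so 187 is reproduced.
- 187 × 1.10 = 205.7, rounded up to 206.

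The point does not turn on these figures. They supply N and the number of teachers: 187 / 50 = 3.7 and 206 / 50 = 4.1 children per teacher.

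**2. The statements side by side.**

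- Teacher and child have not met before (Recruitment overview).
- EF and readiness are measured cross-sectionally, with no later follow-up (The current investigation).
- So a stable teacher trait cannot precede and cause the standing score. What is left is a short-term effect of the sessions on test performance, which cannot be excluded because the order of testing and interaction tasks is not given.
- The Analysis plan nevertheless uses teacher traits to predict these scores.

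Apart from that residual effect, a direct trait-score association has two sources: the way dyads were formed, or chance.

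**3. How large could an artefact be?** The document gives no figure, so these are assumptions. A teacher trait with no effect was simulated against a child outcome: N = 187, 4,000 runs per setting, ordinary correlation test at 5%. ICC is the share of outcome variance common to one teacher's children through pairing; ρ is the correlation of the trait with that common part. Entries are rejection rates.

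| Teachers | ICC | ρ = 0 | ρ = 0.3 | ρ = 0.5 |
|---|---|---|---|---|
| 50 | 0 | 5.0% | – | – |
| 50 | 0.05 | 6.6% | 15% | 32% |
| 50 | 0.10 | 8.2% | 28% | 57% |
| 50 | 0.20 | 11.8% | 45% | 81% |
| 25 | 0 | 4.8% | – | – |
| 25 | 0.05 | 8.2% | 18% | 33% |
| 25 | 0.10 | 12.6% | 29% | 55% |
| 25 | 0.20 | 19.6% | 47% | 76% |

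The Monte Carlo standard error is at most √(0.25 / 4000) = 0.8 percentage points. The ρ = 0 column is a clustering error, which a model with teacher as a cluster can handle. The ρ > 0 columns add confounding. A teacher random effect does not remove that; adjusting for what drives the shared part does.

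**4. Child age as one possible route.** With assumed correlations, induced r = r(trait, age) × r(age, EF):

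- 0.2 × 0.6 = 0.12, R² = 0.014
- 0.3 × 0.7 = 0.21, R² = 0.044
- 0.4 × 0.7 = 0.28, R² = 0.078

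These are unadjusted and for one trait, so they should not be set against the joint R² of 0.09 for 12 predictors. Their use is to show why age belongs in the model.

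**The case against.** Two stronger readings are tempting, and the document does not support them.

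First, a reader might infer that children are paired by recruitment route and teacher choice rather than at random. The recruitment sentence says how participants are found, not how dyads are made. The remark on teachers taking several children concerns how many, not which ones. No pairing rule is stated, and a condensed article may leave one to the full protocol. Random pairing would not rescue the predictor either: it turns a possible artefact into chance, and a chance association is still no evidence of teacher influence.

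Second, a reader might infer that the moderation question is undermined as a whole. It is not. The story quiz, narrative recall and third puzzle phase come after work with this teacher, who can affect them. The point also leaves the behavioural indices alone: a child's own EF can shape how the interaction goes, so an association there is meaningful, if not directional.

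Further objections have weight. Research Question 1 asks about interaction characteristics and is worded as association; teacher traits appear only in the Analysis plan. The correlations and ICCs above have no source in the document, and nothing in it shows that teacher temperament or EF tracks child age. Child characteristics are to be in the same models, and if age is among them the age route closes. All this limits the size of the problem. It does not give a stable trait of a newly met teacher a route to the child's prior skills.

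**Conclusion.** The concern holds as a mismatch between a stated analysis and the stated design: traits of unacquainted teachers are used to predict standing, cross-sectionally measured child scores. It rests on two statements in the article (no prior acquaintance; cross-sectional assessment) and on the premise that EF and readiness scores mainly reflect skills acquired earlier. A small session effect on test performance is the one exception left open.

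The size is unknown. If dyad formation leaves a teacher's children no more alike than others, a naive test keeps its 5% level and the only harm is interpretive. Under the assumed ICCs of 0.05 to 0.20, with ρ of 0 or 0.3, the false-positive rate is about 7% to 47% over 50 or 25 teachers, and higher at ρ = 0.5. The point does not extend to in-session learning, neural coupling or observed interaction behaviour.

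**What to change.** In the Analysis plan:

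- Do not select or interpret teacher traits as predictors of standing EF or school readiness, and keep them out of the variable blocks that are reduced for these models. Retain them only as adjustment covariates for the interaction measures, or report them as a negative control, where a clear association would point to dyad formation rather than teacher influence.
- Use teacher traits as predictors or moderators of interaction behaviour, neural coupling and in-session learning (story quiz and recall, third puzzle phase), and state that the exploratory moderation question refers to these outcomes.
- Adjust the EF and readiness models for child age and recruiting preschool group, with independent recruits as their own category, and allow for clustering by teacher.

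The cost is a paragraph of text, with no extra participants or measurements. Research Question 1 would no longer yield a teacher-trait finding on EF or readiness. Preschool group uses some degrees of freedom; the number of groups is not given, so a random effect may be needed if there are many.

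Optional, and not the core fix: for the remaining dyads, pair at random among the teachers available in a booking window. This removes systematic pairing at the price of some scheduling freedom, but does not make teacher traits valid predictors of standing scores.
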